#### Research variables

4.5.8

In this clinical trial, the designed intervention is considered an independent variable. Pregnant women's concerns in the process of performing AASTs are considered dependent variables. The dependent variables in the quantitative part of the study will be modified and completed after implementing the qualitative part and determining the preferred intervention.

#### Data collection methods

4.5.9

Data from the quantitative study section will be collected using three questionnaires: the Depression, Anxiety and Stress Scale (DASS‐21), a researcher‐made questionnaire for measuring pregnant women's concerns in the process of AASTs, and demographic information and midwifery records questionnaire. The DASS‐21 and the researcher‐made questionnaire will be completed before and 8 to 10 weeks after the intervention by two groups.

The demographic information and midwifery records questionnaire has two sections: demographic‐social information and specifications of AASTs. The demographic‐social information section includes questions about age, education level, employment, economic status, year of marriage and the number of children and will be completed through face‐to‐face interviews upon entering the study. The specifications AASTs section, which will be completed 8–10 weeks after the intervention, includes questions about the timing and results of the AASTs.

The Depression, Anxiety and Stress Scale (DASS‐21) will be used to measure the emotional states of pregnant women. This questionnaire consists of 21 phrases related to the symptoms of negative emotions (depression, anxiety and stress). Each question is scored from zero (does not apply to me at all) to 3 (applies to me very much). As DASS‐21 is the abbreviated form of the main scale (42 questions), the final score of each of these subscales should be doubled. Questions 21, 17, 16, 13, 10, 5 and 3 are related to the depression subscale; questions 20, 19, 15, 9, 7, 4 and 2 are related to the anxiety subscale; and questions 18, 14, 12, 11, 8, 6 and 1 are related to the stress subscale. The validity and reliability of the DASS questionnaire for all three subscales of depression, anxiety and stress have been confirmed with the scores of 0.91, 0.84 and 0.90, respectively (Lovibond & Lovibond, 1996). The validity and reliability of this questionnaire have also been confirmed in Iran (Sahebi et al., 2005; Samani & Joukar, 2007).

To assess the pregnant women's concerns in the process of undergoing AASTs, a questionnaire will be designed by the researcher using the results of the qualitative part and the literature review. The content validation method will be used to confirm the validity of the designed instrument. For this purpose, content validity will be determined qualitatively and quantitatively. In the qualitative method, the questionnaire will be presented to ten experts and faculty members to be examined in terms of grammar, appropriateness and scoring. In addition, the content validity ratio (CVR) and content validity index (CVI) will be used to evaluate the content validity quantitatively. To determine the reliability of the instrument, the test–retest method will be applied; in this method, the modified questionnaire will be presented to twenty qualified individuals twice with a two‐week interval. The reliability of the instrument will then be measured by calculating the correlation coefficient. Based on the results of the first and second stages of the study, other appropriate tools will be used if necessary.

#### The implementation method

4.5.10

The quantitative part of the study is a randomized controlled trial to determine the impact of the designed intervention on reducing pregnant women's concerns for undergoing AASTs. After registering the study in the Iranian Registry of Clinical Trials (IRCT), obtaining the necessary approval from the School of Nursing‐Midwifery and the Ethics Committee and presenting the recommendation letter to hospitals and health centres, affiliated with Tehran University of Medical Sciences, sampling will start at these centres. Initially, continuous convenience sampling will be implemented, that is, all eligible pregnant women will be enrolled in the study after receiving detailed explanations about the purpose of the study, and signing a written consent form. Next, the samples will be divided into intervention and comparison groups using permuted block randomization. The designed intervention will be presented for the intervention group. The control group will not receive any interventions from the research team during the study. Before and 8–10 weeks after the intervention, the status of the participants in the intervention and control groups will be measured using the questionnaire. Finally, the results before and after the intervention will be analysed using inferential statistical methods. A telephone follow‐up will be performed to ensure that all intervention participants receive the intervention and also to ensure the completion of questionnaires in both groups. The participants' data will be stored on a computer and kept confidential. Each participant will have a unique code to avoid double data entry. Participants will be assured of the confidentiality of information.

#### Data analysis

4.5.11

After completing the questionnaires, statistical analysis will be performed using SPSS16.0 on a Windows system (IBM SPSS V.16.0.0). Continuous variables will be presented in the form of mean ±standard deviation (*SD*), and categorical variables will be reported in the form of frequency (percentage). The normality of the variables will be checked using the Kolmogorov–Smirnov test. The chi‐square test or Fisher's exact test, independent sample *t* test and paired *t* test will be used to check the homogeneity of qualitative variables, compare quantitative variables between groups and compare the pre‐/posteffect in each group, respectively.

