#### Sample size

4.5.4

The sample size will be 75 in each group with a confidence interval of 95%, trial power of 80%, Cohen's d of 0.5 and a sample loss of 15%.

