#### Sampling method

4.5.5

In the quantitative part of the study, convenience and continuous sampling will be implemented, in that all eligible individuals will enter the study after receiving a detailed explanation about the purpose of the study and signing an informed consent form. Afterwards, the samples will be divided into intervention and comparison groups using permuted block randomization based on Random Allocation Software considering all possible ways of assigning groups to blocks. The size of the blocks will be randomly selected (e.g., blocks containing 4, 8, 12 and 16 persons equally divided in each group). By selecting blocks randomly, the possibility of disclosing the last allocation in each block will be eliminated (Elkins, 2013; Kang et al., 2008).

This study will be an open‐label trial as masking of intervention is not possible. One of the researchers' colleagues will make the allocation sequence, and the researcher will register the participants and assign them to the intervention and control groups. All participating women will complete the initial questionnaires after randomization. The intervention group will be contacted and informed about the implementation of the intervention.

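### The only between-group test named is an independent t test with no baseline adjustment, although both scores are collected before and after in both arms; ANCOVA would be more precise, provided baseline is taken before allocation is known

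*Protocol article*

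**What the plan says.** Section 4.5.11 (Data analysis) lists the tests and pairs them with purposes in order: they "will be used to check the homogeneity of qualitative variables, compare quantitative variables between groups", and then examine change within each group. Chi-square or Fisher's exact test is for the homogeneity of qualitative variables. The independent-samples t test and the paired t test, in that order, are to "compare quantitative variables between groups and compare the pre‐/posteffect in each group, respectively". No covariate-adjusted model appears anywhere in the article, and the outcome entered into the independent t test (follow-up score or change score) is not stated.

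Section 4.5.9 (Data collection methods) says that the DASS-21 and the researcher-made "questionnaire will be completed before and 8 to 10 weeks after the intervention by two groups". Section 4.5.10 repeats this schedule.

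Section 4.5.4 (Sample size) states: "The sample size will be 75 in each group", "with a confidence interval of 95"%, "trial power of 80"%, and a Cohen's "d of 0.5 and a sample loss of 15"%. No baseline to follow-up correlation is given.

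Section 4.5.5 (Sampling method) describes an open-label trial in which the initial questionnaires are filled in after randomisation. Section 4.5.6 restricts entry to women who already have a significant level of worry about screening.

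**The concern.** Every woman followed up supplies a baseline value of the same score that serves as her outcome. With a continuous outcome, regressing the follow-up score on arm and baseline removes the part of the outcome variance that baseline explains, and corrects the estimate for any chance difference between arms at entry. An independent t test on follow-up scores does neither. On change scores it uses the baseline, but with a coefficient fixed at 1 instead of estimated, which adds noise when the correlation is low. The within-group paired tests also use the baseline, but they do not estimate the difference between arms and recover none of the lost precision.

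At stake is efficiency: a wider confidence interval and lower power than the planned data could give, in a trial with no power to spare after its own 15% loss allowance. The article states the between-group method, so this is not a detail merely left for an analysis plan.

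**Working it through.** **Inputs.** From section 4.5.4: d = 0.5 (so SD = 1), power 80%, 95% confidence, 15% loss, 75 per group. From section 4.5.5: 1:1 allocation, with blocks "equally divided in each group". Two-sided alpha of 0.05 is inferred, since the article does not state sidedness. The baseline to follow-up correlation r is not in the documents; it is an assumption, shown at 0.3, 0.5, 0.6 and 0.7.

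**Step 1: reproduce the plan's figure.** Normal approximation, unadjusted two-sample comparison:

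n = 2(1.960 + 0.842)² / 0.5² = 62.8, so 63 per group; 63 / 0.85 = 74.1, so 75.

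This matches exactly. A one-sided test would need 50, or 59 after inflation, which does not match. The t-based version gives 64, or 76. The plan is therefore sized for an unadjusted two-sided comparison, and is correct for one.

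**Step 2: completers.** 75 × 0.85 = 63.75, taken as 63 per arm.

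**Step 3: residual SD under each analysis** (equal variances at both times):

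- t test on follow-up scores: SD = 1
- t test on change scores: SD = √(2(1 − r))
- ANCOVA: SD = √(1 − r²)

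**Step 4: power.** Two-sample t, 63 per arm, alpha 0.05 two-sided, effect 0.5 / SD:

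| r | Follow-up t test | Change-score t test | ANCOVA | ANCOVA interval narrower than follow-up t test by 1 − √(1 − r²) |
|---|---|---|---|---|
| 0.3 | 79.5% | 65% | 83.1% | 5% |
| 0.5 | 79.5% | 79.5% | 89.5% | 13% |
| 0.6 | 79.5% | 88% | 93.6% | 20% |
| 0.7 | 79.5% | 95% | 97.4% | 29% |

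Example at r = 0.5: √(1 − 0.25) = 0.866; effect 0.5 / 0.866 = 0.577; power 89.5%. The difference detectable with 80% power falls from 0.503 SD to 0.503 × 0.866 = 0.436 SD.

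**Step 5: sensitivity to rounding.** The normal approximation at 63.75 per arm gives 80.6% unadjusted and 84.1%, 90.3%, 94.2% and 97.7% for ANCOVA. The pattern is unchanged.

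**Step 6: is the covariate clean?** The ANCOVA figures assume a baseline unaffected by allocation. Section 4.5.5 places the initial questionnaires after randomisation in an open-label trial, so a woman may know her group when she reports her worry. If that knowledge shifts the score, part of an allocation effect is carried in the covariate and the adjusted difference can be biased. A change score would be affected in the same way.

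**The case against.** The strongest reply is that nothing here is an error. The independent t test is valid under randomisation, the sample size was derived for it, and design and analysis agree. That stands. A reader might infer that the trial is underpowered or that its estimate would be biased, and the documents support neither: the 79.5% at 63 completers is the plan's own 80% after rounding.

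Second, the gain depends on an unknown r. Selecting women for significant worry narrows the baseline range and may lower r, and screening results received before the 8 to 10 week questionnaire could lower it further. This also stands: at r = 0.3 the gain over a follow-up t test is under 4 percentage points of power.

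Third, it is tempting to say that baseline plays no part in the treatment comparison. The article does not support so flat a statement, because a change-score t test is a possible reading. That reading does not rescue the plan: at every r shown ANCOVA has more power, and below r = 0.5 the change score does worse than ignoring baseline.

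Fourth, a reader might infer that the baseline scores are put through significance tests of homogeneity. Section 4.5.11 ties homogeneity checks to qualitative variables, and the scores are quantitative, so no such criticism follows.

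Fifth, adjustment needs a baseline untouched by allocation, which the present order of steps does not guarantee. This is right, and it makes the remedy conditional. It is not a reason to keep the unadjusted test.

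Finally, the article is condensed, and section 4.5.8 leaves the dependent variables open to revision after the qualitative stage. But the article does fix the test, and a baseline-adjusted model suits whichever continuous score is chosen.

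**Conclusion.** The point holds as one of efficiency. The named between-group test makes less use of the baseline than it could, and leaves open which score is tested. With d = 0.5 and 63 completers per arm, ANCOVA would add about 4 percentage points of power over the follow-up t test at r = 0.3, 10 at r = 0.5 and 18 at r = 0.7. Over the change-score t test it would add about 18, 10 and 2 points at the same values. The gain is modest if r is near 0.3, which selection on worry makes plausible.

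These figures rest on a two-sided alpha of 0.05, equal variances at both times, a linear relation between baseline and follow-up, and a baseline unaffected by knowledge of allocation. The last does not follow from the procedure as written and has to be secured. The change is worth making, but the trial remains valid without it.

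**What to change.** In section 4.5.11, name a linear model (ANCOVA) of the 8 to 10 week score on arm and baseline score as the between-group analysis, for the concern score and for each DASS-21 subscale with its own baseline. Report the adjusted mean difference with its 95% confidence interval. This also settles the follow-up or change-score question before data are seen.

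In section 4.5.5, have the initial questionnaires completed before randomisation, or at least before allocation is disclosed to the woman.

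The cost is a sentence of analysis wording and a small change in the order of enrolment steps. No extra women or measurements are needed, and 75 per group can stay.

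### Replace the homogeneity tests and unadjusted t test with a between-arm comparison adjusted for prespecified baseline values

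*Protocol article*

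**What the plan says.** Section 4.5.11 (Data analysis) of the protocol article pairs each test with a use. The tests "will be used to check the homogeneity of qualitative variables, compare quantitative variables between groups", and a paired t test examines change within each arm. Read in order, chi-square or Fisher's exact test serves the homogeneity check, and the independent t test serves the comparison of quantitative variables. No adjusted model is named.

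The arms are formed by permuted blocks of random size, "equally divided in each group" (section 4.5.5), with no stratification factor named. Section 4.5.4 states: "The sample size will be 75 in each group". It bases this on "Cohen's d of 0.5 and a sample loss of 15" per cent.

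The demographic questionnaire (section 4.5.9) "includes questions about age, education level, employment, economic status, year of marriage and the number of children" and is completed on entry to the study. Section 4.5.5 has the initial questionnaires completed after randomisation, in an open-label trial.

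**The concern.** When arms are formed by sound randomisation, differences in characteristics fixed before allocation are due to chance. A significance test of homogeneity therefore tests a hypothesis already known to be true. Whether an imbalance matters for the result depends on its size and on how strongly the characteristic predicts the outcome. The p-value does not measure the second of these, and it measures the first only in relation to sample size. A significant result is an expected chance event. A non-significant one is compatible with an imbalance large enough to move the estimate.

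At stake is the precision and credibility of the between-arm estimate in the particular sample obtained. An unadjusted t test carries any chance imbalance straight into the estimate. Adjustment for baseline values chosen in advance removes that part and usually adds precision.

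**Working it through.** **Inputs.** From section 4.5.4: 75 per arm, d = 0.5, 80% power, 15% loss, and alpha 0.05 from the 95% confidence level (two-sided assumed, as sidedness is not stated). From section 4.5.9: six demographic items. Assumed: independence of the items, and a correlation (rho) of 0.1 to 0.5 between a baseline characteristic and the outcome, because the article gives none.

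**Stated sample size.** n = 2(1.960 + 0.842)² / 0.5² = 62.8, so 63 per arm. Then 63/0.85 = 74.1, so 75. The stated figure reproduces.

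**Chance alarms under correct randomisation.** P(at least one p<0.05) = 1 − 0.95^k.
- k = 3 (education, employment, economic status, the clearly qualitative items): 1 − 0.857 = 14%.
- k = 6 (all listed items): 1 − 0.735 = 26%.

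**Imbalances that pass.** The SE of a standardised difference at 75 per arm is √(2/75) = 0.163.
- The largest non-significant difference is t(0.975; 148) × 0.163 = 1.976 × 0.163 = 0.32 SD. At 63 per arm it is 0.35 SD.
- For a two-category item near 50% prevalence, gaps of up to 16 percentage points pass the chi-square test at 75 per arm (SD 0.5, so 0.16/0.5 = 0.32 SD).
- A 0.25 SD imbalance gives 0.25/0.163 = 1.53, p = 0.13. For a two-category item near 50% this is 0.25 × 0.5 = 12.5 points.

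**Effect on the unadjusted estimate.** Given an imbalance, the shift in outcome SDs is rho × imbalance. With 0.25 SD:

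| rho (assumed) | shift (SD) | share of d = 0.5 |
|---|---|---|
| 0.1 | 0.025 | 5% |
| 0.3 | 0.075 | 15% |
| 0.5 | 0.125 | 25% |

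**What adjustment buys.** ANCOVA multiplies the residual variance by 1 − rho². The evaluable number needed for 80% power changes as follows:
- rho 0.1: 63 × 0.99 = 62.4, so 63 (no gain).
- rho 0.3: 63 × 0.91 = 57.3, so 58.
- rho 0.5: 63 × 0.75 = 47.3, so 48.

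With 63 evaluable per arm, power at d = 0.5 rises from 80% to about 84% (rho 0.3) or 90% (rho 0.5).

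**The case against.** The strongest reply is that section 4.5.11 says little and should not be made to say more. Several parts of that reply stand.

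- **Scope.** The homogeneity wording attaches to qualitative variables only. Age, year of marriage and number of children are naturally quantitative, so 14% is the literal figure and 26% an upper case. These three items are also likely to be related, so independence is only an approximation.
- **No decision rule.** A reader might infer that the tests certify the arms as comparable, or trigger adjustment chosen after seeing the data. The article says neither. It attaches no consequence to a significant or non-significant result, so deleting the tests would not by itself change any effect estimate.
- **No bias on average.** A reader might infer that the planned t test is invalid. It is not: over all randomisations it is unbiased and keeps its 5% level. The shifts above are conditional on the imbalance seen.
- **Not the only protection.** Permuted-block randomisation is the main guard against systematic imbalance, and section 4.5.11 already provides descriptive summaries.
- **Power of the check.** It is tempting to quote the test's power to detect a true baseline difference between arms. Under randomisation no such true difference exists, so that figure has no bearing here.
- **Detail left elsewhere.** A covariate list commonly sits in the full protocol or SAP, and section 4.5.8 says the dependent variables will be completed after the qualitative stage. The absence of a list is therefore not the finding.

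The reply does not rescue the stated choice. The article fixes a homogeneity test that cannot answer the question of balance, and an unadjusted comparison where a better one is available from data already planned.

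**Conclusion.** The point holds as a minor improvement of method. The homogeneity p-values are uninformative: a 14% chance of a false alarm on the literal reading, up to 26% if all six items are tested, and imbalances of up to about 0.32 SD passing at 75 per arm. The part worth acting on is the unadjusted comparison. A non-significant 0.25 SD imbalance shifts its estimate by 5% to 25% of the design effect for an assumed correlation of 0.1 to 0.5. At the low end of that range the matter is slight, and nothing in the article shows which listed items are prognostic. The sample size of 75 per arm is unaffected.

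**What to change.** In section 4.5.11:

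1. Remove the homogeneity tests. Keep the baseline table by arm with means, SDs, counts and percentages; standardised differences may be added.
2. Replace the independent t test for the between-arm comparison with a linear model (ANCOVA) containing arm and a short prespecified list of baseline values already collected, for example age and number of children. Enter them whatever the observed balance. Allocation cannot alter these two, so they are safe covariates. Gestational age at entry appears only as an eligibility limit in section 4.5.6, not among the items listed in section 4.5.9. It would have to be confirmed as recorded before being named.
3. Enter the baseline concern score too, provided the initial questionnaire is completed before allocation. Section 4.5.5 now places it after open-label randomisation, where knowledge of the assigned arm could affect the answers, so that order would need to change first.

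The cost is a change of wording and a few degrees of freedom, with no new data or participants. Including the baseline concern score also requires the initial questionnaire to be moved ahead of allocation.

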Regardless of the stress and anxiety associated with pregnancy‐related tests and ultrasound examinations, pregnancy alone can cause stress and anxiety in many women (Georgsson Öhman et al., 2004). Pregnant women might experience varying degrees of anxiety during pregnancy. In this regard, many women experience emotional distress during the first and third trimesters (Georgsson Öhman, 2005). It is very important to address maternal concerns during pregnancy because the mental state of pregnant mothers has a relationship with the occurrence of low birth weight and cesarean delivery (Bastani et al., 2006; van Bussel et al., 2009; Matthey et al., 2003; Robertson et al., 2004). These anxieties and worries affect the mothers' sleep quality, as well as the quality of life, and can have such psychological consequences as postpartum depression (Jomeen, 2004).

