#### Inclusion criteria

4.5.6

Pregnant women with a gestational age of fewer than 11 weeks that apply for completing the initial prenatal recordLack of Down syndrome and other anomalies in the foetus in previous pregnanciesNo history of known mental disorders or consumption of psychiatric drugsPregnant women with a significant level of worry about AASP

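### Within-arm paired t tests are planned beside a valid between-arm test, with no statement of which decides effectiveness; in women selected for worry they do not test the intervention

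*Protocol article*

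**What the plan says.** All references are to the protocol article.

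- **Data analysis (4.5.11).** One sentence lists the tests by purpose. The independent t test is to "compare quantitative variables between groups". The paired t test is for the pre- and "posteffect in each group, respectively". The sentence does not rank them.
- **The implementation method (4.5.10).** The inference is described only in before/after terms: "Finally, the results before and after the intervention will be analysed using inferential statistical methods". The comparator is untreated by the team: "The control group will not receive any interventions from the research team during the study".
- **Inclusion criteria (4.5.6).** Entry is limited to women with substantial worry about the screening process and to "Pregnant women with a gestational age of fewer than 11 weeks". No instrument or threshold for worry is given, and section 4.5.7 says the criteria will be revised after the qualitative stage.
- **Data collection methods (4.5.9).** The DASS-21 and the concerns questionnaire are "completed before and 8 to 10 weeks after the intervention by two groups".
- **Sampling method (4.5.5).** "All participating women will complete the initial questionnaires after randomization".
- **Sample size (4.5.4).** 75 per group, from 80% power, 95% confidence, Cohen's d of 0.5 and 15% loss.

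**The concern.** A paired t test inside one arm asks whether the mean score moved. In this trial it can move without the intervention for two reasons.

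1. *Selection.* Women chosen because their worry is high will on average score lower when measured again, if the score used for selection is also the starting point of the comparison.
2. *Time.* A woman who enters at 10 weeks and is followed 8 to 10 weeks later is measured at 18 to 20 weeks or later, depending on how long the intervention lasts. The Introduction says that "many women experience emotional distress during the first and third trimesters", so the two readings may fall in periods with different background distress.

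The control arm exists to remove both influences, and a within-arm test leaves it out. Comparing verdicts across arms (significant in one, not in the other) does not repair this, because it is not a test of the difference between arms. As neither test is named as decisive, either pattern could be offered as evidence of effectiveness for an intervention that the Discussion hopes will inform health policy.

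**Working it through.** **1. What the trial was sized for.** For two means with d = 0.5, two-sided alpha 0.05 and 80% power:

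n = 2(1.960 + 0.842)² / 0.5² = 62.8, so 63 per arm; 63 / 0.85 = 74.1, so 75.

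The exact t calculation gives 63.77, and 63.77 / 0.85 = 75.02. The stated 75 reproduces as a two-sample comparison, so the trial is sized for the between-arm test.

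**2. Assumptions for the within-arm test.** From the documents: equal groups, and about 63 evaluable women per arm after 15% loss. Not in the documents, so assumed: no intervention effect, a score with SD 1 in unselected women, entry of the top 75%, 50% or 25%, and pre/post correlation r from 0.5 to 0.9. Each setting was simulated 4,000 times, with a two-sided 5% paired t test in each arm. A significant *fall* then has a nominal rate of 2.5%.

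**3. Selection on the baseline score itself.** With baseline mean m and variance v among selected women:

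- expected fall = (1 − r)m
- variance of the change = (1 − r)²v + (1 − r²)

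For the top half, m = 0.798 and v = 0.363. At r = 0.7 the fall is 0.3 × 0.798 = 0.24 SD and the SD of change is √(0.09 × 0.363 + 0.51) = 0.737. The noncentrality is (0.239 / 0.737) × √63 = 2.58, which agrees with the simulated 72%.

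Proportion of arms with a significant fall:

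| Entry | r = 0.5 | r = 0.7 | r = 0.8 | r = 0.9 |
|---|---|---|---|---|
| Top 25% | 100% | 99% | 90% | 62% |
| Top 50% | 93% | 72% | 52% | 29% |
| Top 75% | 42% | 26% | 18% | 12% |

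The between-arm t test on follow-up scores was significant in 4.3% to 5.4% of these trials.

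**4. A separate worry screen before baseline.** Eligibility is settled before randomisation and the questionnaires come after it, so the screen may be an earlier reading.

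- Screen–baseline correlation 0.85, with further decay to follow-up: 40% to 99% for top-half or top-quarter entry at r = 0.5 to 0.8.
- All three readings equally correlated: the regression is complete by baseline, and the rate is the nominal 2.5% or so.

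**5. The misleading pattern.** If an arm shows a significant fall with probability p under the null, and the arms are independent, then intervention significant and control not has probability p(1 − p). For top-half entry:

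- r = 0.5: 0.93 × 0.07 = 6.5%
- r = 0.7: 0.72 × 0.28 = 20%
- r = 0.8: 0.52 × 0.48 = 25%
- r = 0.9: 0.29 × 0.71 = 21%

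The maximum of p(1 − p) is 25%. If p were the nominal 2.5%, the pattern would occur in 0.025 × 0.975 = 2.4% of trials.

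**6. Time alone, no selection.** For a natural fall of δ SD, the noncentrality is δ√63 / √(2(1 − r)). For δ = 0.2 the paired test is significant in 35% (r = 0.5) or 52% (r = 0.7) of arms; for δ = 0.3, in 65% or 86%. The size of δ is an assumption.

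**The case against.** The strongest reply is that the right test is already in the plan. The same sentence of 4.5.11 contains the independent t test, 4.5.4 is sized for it, randomisation makes it valid, and the paired tests do not bias it. All of that stands. A reader might infer that the trial has no sound efficacy test, and the documents do not support that.

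A second reply is that an article may leave the ranking of analyses to a fuller document. That also stands, so the absence of a ranking is not an error by itself. The point rests on what the article does state: it commits to an inferential within-arm test of the pre/post effect, in a population selected on worry.

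A third reply is that the size is uncertain. A reader might infer that a significant fall is simply to be expected with no effect. The documents give no cut-off, no correlation and no screening instrument, the worry criterion is provisional, and the rate runs from nominal to about 100%. A reader might also infer that worry falls in both arms once screening results arrive. The documents do not say so. Baseline precedes the 11-week opening of the screening window, and the Background describes anxiety while awaiting diagnostic results, so worry could equally rise.

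Lastly, under the null half of the trials in which exactly one arm is significant favour control. Only the half that favours the intervention is counted above.

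**Conclusion.** The point holds in limited form. A valid between-arm test is planned, but within-arm tests are planned beside it and the article does not say which decides effectiveness. That a within-arm p-value cannot separate the intervention from selection and time needs no numerical assumption.

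How often it would mislead does depend on assumptions. With selection on the baseline score, the rate is substantial for top-half or top-quarter entry with r up to about 0.8, and modest for a loose cut. Regression to the mean contributes nothing if an earlier screen has absorbed it all, although a natural fall in worry could still do so. It is worth correcting before analysis because it closes an invalid route to an efficacy claim at almost no cost.

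**What to change.** In 4.5.11, state that effectiveness is judged only on the between-arm difference in follow-up concern score, adjusted for the baseline score by ANCOVA and reported with a 95% CI. Report mean change per arm descriptively, without p-values, and bring the before/after sentence in 4.5.10 into line.

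The baseline adjustment is a gain in precision from data already collected; the unadjusted t test is valid without it. One condition applies. Because the trial is open-label and the first questionnaires follow randomisation, the adjustment is safe only if women complete them before learning their group.

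The cost is a sentence or two of text and the loss of the within-group p-values. No extra participants or measurements are needed.
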